#### Inclusion criteria

Patients will be eligible for the study if they:
Male or female patients aged 18–65 years.Patients diagnosed with peripheral facial paralysis ≥3 months before screening.Patients with H-B Grade ≥III.Patients with atrophic facial expression muscles as revealed by B-mode ultrasonography. The muscle thickness of the affected side/healthy side ≤ 90%.

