### Sample size

The sample size was based on previous similar studies [26], and advice from an expert group. The formula below was used to determine the sample size in each group (28 participants) (alpha (significance level), power (1-beta), dropout rate, and group sample ratio were 0.05, 0.90, 10%, and 1:1, respectively). σ indicates standard deviation (23.30) and d represents the mean difference between the two groups (21.54):
$$ \mathrm{n}=2{\sigma}^2{\left({\mathrm{Z}}_{\alpha /2}+{\mathrm{Z}}_{\beta}\right)}^2/{\mathrm{d}}^2 $$

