### Outcome measures

#### Primary outcome measure

As the primary outcome measure, B-mode ultrasonography will be used to measure facial expression muscle thickness ratio of affected/healthy side.

The operator will use the muscle thickness of both sides of frontal muscle and depressor anguli oris muscle to calculate the affected/healthy side ratio.
Four test points will be on both sides of the frontal muscle and depressor anguli oris muscle (Fig. 5).Detailed procedure: The examination will be performed in a quiet room with low light and at constant room temperature. Participants will lay still for 5 minutes before test. During measurements, participants will lay on the examination bed on their back, keeping their mouths closed and relaxed without making any other expression. An experienced B-mode ultrasonographer will take all measurements.Equipment: GE Logiq9 real-time ultrasonic diagnostic instrument will be used to obtain the measurements. M12L will be used as the probe at a frequency of 5~14MHz and a main frequency of 10MHz.Timepoint of the test: Two measurements will be taken: pre-treatment and at follow-up 1 (week 10).

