### Data processing and statistical analysis

Following the intention-to-treat principle, data processing and analysis will be performed at the Clinical Evaluation and Analysis Centre of The First Affiliated Hospital of Zhejiang Chinese Medical University. These analyses will be performed on the base of a full analysis set (FAS) and a per-protocol set (PPS). All efficacy analyses will be performed using a FAS, which will consist of all patients who passes the randomized stage and who receives at least one intervention. Last observation carried forward (LOCF) analysis will be used for missing data imputation. The PPS will be considered as a supportive analysis. The results of FAS and PPS analyses will be compared to ensure that the results are consistent. A generalized linear mixed-effect model will be used for sensitivity analysis via the PPS. A subgroup analysis will be conducted following the Kellgren–Lawrence grade.

Quantitative results will be described by the mean, standard deviation, median (quartile 3–1, Q3–Q1), minimum, and maximum, while qualitative results will be expressed as total number and percentages. Grade results with rank meaning will be described via both quantitative and qualitative methods.

The chi-square test will be used to compare the primary outcomes between the two groups. The Wilcoxon rank-sum test will be used to compare ranked data and the independent samples t-test for secondary outcome measures to analyze continuous variables. The incidence of adverse events will be determined and compared between the two groups for safety outcomes. A p-value of <0.05 will be considered statistically significant. SPSS Statistics V.22.0 will be used for all analyses. An interim analysis will be conducted when 50% of the randomized patients completed the primary outcome measurement.

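### The primary outcome is a continuous thickness ratio, but the plan tests it with a chi-square test that fits neither the endpoint nor the sample size calculation

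*Protocol article*

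**What the plan says.** - **Endpoint.** Under the primary outcome measure, the protocol article says "B-mode ultrasonography will be used to measure facial expression muscle thickness ratio of affected/healthy side". On timing it says "Two measurements will be taken: pre-treatment and at follow-up 1 (week 10"). The Abstract and the Study design section describe the outcome as the change in this ratio.
- **Test for the primary outcome.** The section on data processing and statistical analysis says "The chi-square test will be used to compare the primary outcomes between the two groups".
- **Other methods in that section.** It names "the independent samples t-test for secondary outcome measures to analyze continuous variables" and the Wilcoxon rank-sum test for ranked data. A generalized linear mixed-effect model appears only as a sensitivity analysis on the per-protocol set.
- **Sample size.** The inputs are given as "alpha (significance level), power (1-beta), dropout rate, and group sample ratio were 0.05, 0.90, 10%, and 1:1, respectively", with an SD of 23.30, and "d represents the mean difference between the two groups (21.54"). The formula is the one for two means, with the normal quantile taken at α/2.
- **Thresholds on the ratio.** There is only one, in the inclusion criteria: "The muscle thickness of the affected side/healthy side ≤ 90" per cent. It decides who enters the trial. It does not define a response.

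**The concern.** A chi-square test compares counts in categories, and a thickness ratio has no categories until somebody creates them. The article does not say where the ratio would be cut, or whether the cut would apply to the week-10 value or to the change. The analyst is left to choose a cut-off, possibly after seeing data, or to depart from the published plan. Either choice exposes the confirmatory result to challenge.

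The named test is also not the one for which the trial was sized. Splitting a continuous measurement into two groups discards information, so the stated 90% power does not carry over to a chi-square test on the same patients. In addition, the baseline ratio is measured in every patient but has no stated role in the between-group comparison.

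**Working it through.** **Inputs.** From the Sample size section: d = 21.54, σ = 23.30, α = 0.05 two-sided, power 0.90, dropout 10%, allocation 1:1. The standardised difference is 21.54/23.30 = 0.924. The article gives no cut-off, so a range is assumed.

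**Step 1: the plan's own figure.** n = 2σ²(z₀.₉₇₅ + z₀.₉₀)²/d² = 2 × 23.30² × (1.960 + 1.282)²/21.54² = 24.6, so 25 per arm. Allowing for dropout, 25/0.9 = 27.8, so 28 per arm. This matches the article and confirms that the calculation is for a comparison of means.

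**Step 2: power of the comparison of means.** With m per arm the noncentrality is 0.924 × √(m/2), which is 3.27 at m = 25. By the noncentral t distribution, power is 89.3% with 25 per arm and 92.5% with 28.

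**Step 3: power of a chi-square test on the same data after a split.** Assume normal data with equal SDs. For a cut-off c, in SD units above the control mean, the response proportions are 1 − Φ(c) in the control arm and 1 − Φ(c − 0.924) in the active arm. Power is by exact binomial enumeration of the Pearson test at 25 per arm.

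| Cut-off (SD above control mean) | Control vs active | Power | With continuity correction |
|---|---|---|---|
| −0.5 | 69.1% vs 92.3% | 58.8% | 38.6% |
| 0 (control mean) | 50.0% vs 82.2% | 70.8% | 58.3% |
| 0.462 (midway, best) | 32.2% vs 67.8% | 76.9% | 67.0% |
| 0.924 (active mean) | 17.8% vs 50.0% | 70.8% | 58.3% |
| 1.5 | 6.7% vs 28.2% | 56.2% | 34.5% |
| 2.0 | 2.3% vs 14.1% | 31.3% | 8.0% |

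Cut-offs close to the midpoint (0.25 and 0.7) give 75–76%. With all 28 per arm evaluable, the best cut-off gives 76.5%.

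**Step 4: size needed to recover 90% at the best cut-off.** The usual two-proportion formula, with average proportion 0.5, gives n = [1.960 × √(2 × 0.5 × 0.5) + 1.282 × √(0.322 × 0.678 + 0.678 × 0.322)]²/(0.678 − 0.322)² = 39.3, so 40 evaluable. Then 40/0.9 = 44.4, so about 45 randomised per arm against 28 planned. Cutting at either arm's mean needs 44 evaluable, or 44/0.9 = 48.9, so 49 randomised.

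**Step 5: what baseline adjustment might add.** The baseline/week-10 correlation ρ is not given, so 0.3, 0.5 and 0.7 are assumed, with 25 per arm.
- If 23.30 is the SD of the week-10 ratio, the residual SD is 23.30 × √(1 − ρ²) = 22.2, 20.2, 16.6. Power is about 92%, 96%, 99%.
- If 23.30 is the SD of the change, with equal variances at both visits, the residual SD is 23.30 × √((1 + ρ)/2) = 18.8, 20.2, 21.5. Power is about 98%, 96%, 93%.

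**The case against.** The strongest reply accepts the mismatch and disputes its size and the extent of the remedy.

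- **Source of the SD and difference.** The Sample size section attributes its inputs to earlier similar work and expert advice, and does not say that 23.30 and 21.54 refer to the thickness ratio. This stands. The power figures illustrate a standardised difference of 0.924 and are not the established power of this endpoint.
- **The chi-square powers are hypothetical.** No split is specified, so the loss depends on the cut-off assumed and on normality with equal SDs. This also stands, but it does not help the plan. Power falls at every cut-off tried, and the lack of a defined split is part of the defect.
- **Baseline adjustment is a preference.** A t-test on the change would agree with the sample size formula, and covariates are often left to an analysis plan that is not shown here. This is fair. The ANCOVA gain rests on assumed correlations, and adjustment for disease duration is optional.
- **Two muscles are measured.** The article does not say whether the frontal and depressor anguli oris ratios are combined or analysed separately, so changing the test alone does not fix a single comparison. This stands as a point to settle in the same edit.

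An unseen analysis plan does not remove the main point. The article does not leave the primary test open. It names one, and that test does not suit the endpoint.

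**Conclusion.** The concern holds and must be corrected before any analysis of the primary outcome. The mismatch is a matter of text and needs no assumptions: the test for categories is attached to a continuous primary outcome, the t-test is attached to secondary outcomes, and the trial is sized on a difference of means.

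The size of the loss is conditional. If the stated SD and difference apply to the ratio and the data are normal with equal SDs, moving from a t-test to a chi-square test with 25 evaluable patients per arm takes power from 89% to 77% at best. It falls to 71% if the cut-off is at either arm's mean, and to 56% at 1.5 SD above the control mean. A continuity correction lowers each chi-square figure further.

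**What to change.** Replace the sentence that assigns the chi-square test to the primary outcome with wording such as:

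> The week-10 affected/healthy thickness ratio will be compared between groups by ANCOVA with the baseline ratio as covariate, reporting the adjusted mean difference with its 95% CI.

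In the same edit:
- State whether the primary ratio is a single figure combining the two muscles, or one named muscle, so that there is one primary comparison.
- Optionally add disease duration as a covariate, since the Discussion says recovery differs with disease course.
- Keep chi-square or Fisher tests for categorical data such as adverse event incidence.

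An unadjusted t-test on the change would be acceptable and would match the sample size formula directly. If a responder analysis is really intended as primary, its cut-off must be prespecified and the trial re-sized.

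The cost is one sentence plus the formal application that the section on protocol modification requires. Both ratios are already collected, so there are no new measurements or patients. The change should be dated before the interim analysis, which is planned once half of the randomised patients have the primary outcome, so that the choice cannot depend on the data.

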### Allocation

After completing a baseline evaluation, eligible participants will be randomly assigned to either the intervention or the sham-controlled group in a 1:1 ratio by an independent investigator. Subjects in the intervention group will receive TEA treatment, whereas the subjects in the sham-controlled group will receive the sham treatment. Random numbers will be generated by a statistician from the Clinical Evaluation and Analysis Centre of The First Affiliated Hospital of Zhejiang Chinese Medical University using SPSS for Windows (Version 22.0; SPSS Inc., Armonk, NY, USA). Sealed opaque assignment envelopes were used for allocation concealment. Those envelopes will be stored in a locker and the key kept by the clinical research coordinator (CRC). CRC will offer the envelopes that correspond to the group allocation to the acupuncturist after completion of recruitment.

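### The primary outcome is a continuous thickness ratio, and the trial is sized on a difference in means, yet the plan tests it with a chi-square test and defines no categories

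*Protocol article*

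**What the plan says.** Three sections of the protocol article bear on this point.

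- **Primary outcome measure:** "B-mode ultrasonography will be used to measure facial expression muscle thickness ratio of affected/healthy side". The ratio is calculated from thickness measured on both sides of the frontal and depressor anguli oris muscles, before treatment and at week 10. It is a measured, continuous quantity.
- **Sample size:** the formula is the two-sided one for two means. The text there reads "d represents the mean difference between the two groups (21.54", the SD is 23.30, and "alpha (significance level), power (1-beta), dropout rate, and group sample ratio were 0.05, 0.90, 10%, and 1:1, respectively". The result is 28 per group.
- **Data processing and statistical analysis:** "The chi-square test will be used to compare the primary outcomes between the two groups". The same paragraph gives the independent-samples t-test to continuous secondary outcomes and the Wilcoxon rank-sum test to ranked data.

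No section turns the ratio into categories. The only threshold is the 90% limit under Inclusion criteria, which is an entry condition and not a definition of response. The generalized linear mixed-effect model appears only as a sensitivity analysis in the per-protocol set, so it does not replace the primary test.

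**The concern.** A chi-square test compares counts across categories. It uses neither the size nor the order of a measured ratio, and it does not estimate the difference in means on which the trial was sized. Whoever runs the analysis has two ways to follow the sentence, and a third that departs from it:

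- **Cross-tabulate the recorded ratios.** The result then carries almost no information about treatment.
- **Choose a cut-off and compare proportions.** The cut-off is not prespecified, so it could be picked after the data are seen, which puts the type I error at risk. The power is also no longer the stated 90%.
- **Use a t-test without saying so.** This is an undocumented departure from the published primary analysis.

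The trial's main conclusion depends on this one test.

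**Working it through.** **Inputs.** From the Sample size section: two-sided alpha 0.05, power 0.90, SD 23.30, difference 21.54, dropout 10%, 1:1 allocation. The standardised difference is 21.54/23.30 = 0.924.

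**1. The plan's own figure.** n = 2 × 23.30² × (1.960 + 1.2816)² / 21.54² = 24.59, rounded up to 25 per group. Then 25/0.9 = 27.8, rounded up to 28. The stated size is reproduced, so it rests on a comparison of means.

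**2. Power of the comparison that was sized.** With a two-sample t-test, the noncentrality is 0.924 × √(n/2).

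- 25 per group: 3.27 on 48 df, power 89.3%.
- 28 per group: 3.46 on 54 df, power 92.5%.

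**3. Chi-square on the ratios as recorded.** If all N values differ, each value forms a category holding one patient. With equal arms the expected count in each of its two cells is 0.5, so the category contributes 2 × 0.5²/0.5 = 1. The statistic is therefore always N on N − 1 df.

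- N = 50: p = 0.43.
- N = 56: p = 0.44.

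Neither depends on the treatment effect. Rounding creates ties and changes this only slowly. Simulations used 28 per arm, the planned effect and an assumed sham mean of 70, with 2000 trials for each rounding. Rejection at 5% occurred in 0 trials with whole-percent rounding, about 13% with rounding to 5 points and about 33% with rounding to 10 points.

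**4. Chi-square on a dichotomised ratio.** Assume normal outcomes with a common SD. The best cut lies midway between the two means. The proportions above it are Φ(0.462) = 67.8% and 32.2%. The table gives power by exact enumeration. The cut positions are assumed, because the document gives none.

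| Cut, distance from midpoint | Proportions above cut | 25 per arm: Pearson | 25 per arm: Yates / Fisher | 28 per arm: Pearson | 28 per arm: Yates / Fisher |
|---|---|---|---|---|---|
| 0 | 67.8% v 32.2% | 76.9% | 67.0% / 67.0% | 76.5% | 66.9% / 67.3% |
| 0.5 SD | 48.5% v 16.8% | 70.0% | 57.0% / 57.1% | 74.4% | 62.8% / 65.0% |
| 1 SD | 29.5% v 7.2% | 57.5% | 36.6% / 41.8% | 60.6% | 44.4% / 44.4% |
| 1.5 SD | 15.0% v 2.5% | 33.8% | 9.5% / 11.0% | 39.5% | 13.5% / 13.5% |

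Exact Pearson power at the best cut does not rise from 25 to 28 per arm because the counts are discrete. The normal approximation gives 72.5% and 77.5%.

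**5. Size needed for 90% power at the best cut.** The unpooled formula gives 36.2 per arm (37), the pooled formula 39.3 (40), and exact Pearson enumeration 39. The plan provides for 25 evaluable per arm. Allowing for 10% dropout, 40/0.9 = 44.4, so 45 per arm or 90 in total, against 56.

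**The case against.** The strongest objections concern emphasis and do not reach the core.

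- **Nobody would cross-tabulate 56 raw ratios.** This is fair as a prediction. The constant p-value also needs distinct values, and coarse rounding restores some power. The realistic harm is the missing cut-off and the lost power, and that harm stands.
- **It may be a drafting slip.** The same section names a Kellgren–Lawrence subgroup, which matches nothing else in the protocol, so text may have been carried over. That would explain the sentence without making it right.
- **The full analysis set with last observation carried forward could keep up to 28 per arm.** This softens the loss at off-centre cuts, as the table shows. At the best cut Pearson power is still 76.5%, against 92.5% for the t-test.
- **Statisticians are to be blinded.** This makes a cut-off chosen with knowledge of the arms less likely, but the choice remains open.
- **The variable behind 23.30 and 21.54 is not named.** This is true, and reading them as the thickness ratio is an inference. The power loss depends only on the standardised difference of 0.924, not on the units.
- **The abstract and Study design section speak of changes in the ratio, not the week-10 value.** A week-10 comparison, with baseline adjustment if wanted, targets the same between-arm effect in a randomised trial.

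**Conclusion.** The concern holds, and the primary test is wrong as written. This is not a detail left to a fuller document, because the article names the test and the test contradicts both the outcome and the sample size.

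On no workable reading does it deliver the stated 90% power. With a single cut placed as favourably as possible and 25 evaluable per arm, power is about 77% uncorrected and 67% with Yates or Fisher. Those figures are about 12 and 22 points below the t-test's 89%. A cut 1 SD away gives 58% uncorrected and 37–42% corrected or by Fisher. The power figures rest on normality, equal SDs, the planned effect and assumed cut positions. The constant p-value for distinct ratios needs none of these.

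The sample size arithmetic is sound and needs no change if means are compared.

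**What to change.** In Data processing and statistical analysis, replace the chi-square sentence for the primary outcome. The new sentence should compare the mean week-10 affected/healthy thickness ratio between arms, by t-test or by a linear model that may adjust for the baseline ratio, and report the difference with a 95% confidence interval. Two muscles are measured and the sentence speaks of primary outcomes in the plural, so it should also say which ratio or combination it refers to.

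Keep chi-square or Fisher's test for categorical data such as adverse event incidence. If a responder analysis is wanted, fix its cut-off now and label it supportive. Making it primary would mean recalculating the sample size.

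The cost is one amended sentence, plus the formal application and registry update if this counts as a change under Modification of the protocol. No new data are needed. The article reports ten patients under treatment and plans an interim analysis once half of the randomised patients have the primary measurement, so the change should be dated before that analysis and before any unblinded look.

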**Methods:**

This is a patient-assessor blinded, randomized, sham-controlled trial. A total of fifty-six eligible patients will be randomly divided into TEA (n=28) and sham TEA (STEA) (n=28) groups. Both groups will receive TEA or STEA treatment at the frontal muscle and the depressor anguli oris muscle, at one predefined points once a week for eight weeks. Additionally, both groups will receive traditional acupuncture treatment at ten acupoints (GB20, LI4, LR3, GB12, ST7, SI18, LI20, BL2, SJ23, ST4) twice a week for eight weeks as a concurrent treatment. B-mode ultrasonography will be used to assess the changes in facial expression muscle thickness ratio of the affected/healthy side at baseline and at 10 weeks after screening, as the primary outcome. House-Brackmann Grade and lip mobility score will be measured and analyzed at baseline and 4, 8, 10, and 12 weeks after screening, as secondary outcomes.

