#### Secondary outcome measures

House-Brackmann Grade, the severity of facial paralysis will be assessed using the HB Grade at weeks 0, 4, 8, 10, and 12. Grade I (normal function) to VI (total paralysis) will be evaluated based on the facial function at rest and with effort.Lip mobility score. Lip mobility will be assessed using the lip-length index (LL-index) and snout index (S-index) at weeks 0, 4, 8, 10 and 12. The LL-index will be calculated by determining the percentage change in lip length between grinning and resting. The S-index will be calculated by determining the percentage change in lip length between puckering and resting. Lip length will be measured by determining the inter-commissural length.

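### Secondary outcomes are taken at baseline and four later visits, but their main tests are two-sample tests with no baseline covariate and no main visit named

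*Protocol article*

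**What the plan says.** All references are to the protocol article.

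- **Secondary outcome measures.** For H-B grade, "the severity of facial paralysis will be assessed using the HB Grade at weeks 0, 4, 8, 10, and 12". For the lip measures, "Lip mobility will be assessed using the lip-length index (LL-index) and snout index (S-index) at weeks 0, 4, 8, 10 and 12". That makes three measures, each with a baseline and four later values per patient.
- **Abstract, Methods.** These outcomes are "measured and analyzed at baseline and 4, 8, 10, and 12 weeks after screening, as secondary outcomes", so analysis at several visits is stated, not inferred. Study design repeats this.
- **Data processing and statistical analysis.** The tests are given in one sentence: "The Wilcoxon rank-sum test will be used to compare ranked data and the independent samples t-test for secondary outcome measures to analyze continuous variables". The threshold is "A p-value of <0.05 will be considered statistically significant". The section names no main visit, overall contrast, baseline covariate or multiplicity rule for these outcomes. It does not say whether the t-test is run on raw values or on change from baseline.
- **Same section.** Efficacy analyses use the full analysis set (FAS). A generalized linear mixed-effect model is named only for a sensitivity analysis on the per-protocol set (PPS), with no outcome or terms given.

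**The concern.** Each patient supplies a baseline and four correlated later values. A two-sample t-test or rank-sum test compares one number per patient and has no place for a covariate. The plan does name a model that could use the baseline and all visits, but assigns it to the supportive population and a sensitivity role.

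The baseline is likely to carry information here. Entry requires only H-B grade III or worse, so grades III to VI can enter, and the Discussion says the study is not designed as a stratified one. The Discussion also treats recovery of muscle function as essential to judging the treatment, and these are the trial's only functional measures.

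Two separate things are at stake:

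- precision given up at any one visit, because the baseline is not modelled;
- four answers per outcome with nothing to say which one counts.

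**Working it through.** **Inputs from the article.** Sample size gives "power (1-beta), dropout rate, and group sample ratio were 0.05, 0.90, 10%, and 1:1, respectively" (the first figure, 0.05, is alpha), then "σ indicates standard deviation (23.30) and d represents the mean difference between the two groups (21.54"), and uses its formula to "determine the sample size in each group (28 participants"). The significance level is 0.05 per test, with four post-baseline visits.

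**Inputs assumed.** The article gives no correlation between visits. I take a common correlation rho of 0.3, 0.5 and 0.7, and up to 0.9 for the error rate. A true difference of 0.5 SD is also an assumption, because the article gives no effect size for the secondary outcomes.

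**1. The article's own figure.** n = 2 × 23.30² × (1.960 + 1.282)² / 21.54² = 24.59, rounded up to 25. Allowing for 10% dropout, 25 / 0.9 = 27.8, rounded up to 28. The stated 28 per group is reproduced, so about 25 evaluable patients per arm is a fair basis for what follows.

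**2. Power at a single visit.** In SD units, the residual SD is:

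- raw value: 1
- change from baseline: √(2(1 − rho))
- ANCOVA: √(1 − rho²)

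Simulated power with 25 per arm, a 0.5 SD difference and two-sided 0.05:

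| rho | t-test, raw | t-test, change | ANCOVA |
|---|---|---|---|
| 0.3 | about 41% | 31% | 43% |
| 0.5 | about 41% | 41% | 51% |
| 0.7 | about 41% | 61% | 67% |

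A noncentral-t calculation with the SDs above agrees within about one point (ANCOVA 44%, 52% and 68%). ANCOVA is the best of the three in every row. Change scores are worse than raw values below rho 0.5 and better above it.

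**3. Any of four visits significant when there is no effect.** If the visits were independent, 1 − 0.95⁴ = 18.5%, the upper reference value. Simulated t-tests on raw values with 25 or 28 per arm:

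| rho between visits | at least one p<0.05 |
|---|---|
| 0.3 | about 17-18% |
| 0.5 | about 16% |
| 0.7 | about 13% |
| 0.8 | about 11-12% |
| 0.9 | about 9-10% |

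If change scores are tested, two changes from the same baseline have covariance 1 − rho and variance 2(1 − rho). Their correlation is therefore 0.5 whatever rho is, and the rate is about 16%. One pre-named visit, or one overall test, gives 5%.

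**4. Would the average over the four visits be a better main estimate?** Its baseline-adjusted variance is (1 + 3rho)/4 − rho², which is 0.375 at rho 0.5 and 0.285 at rho 0.7.

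- *Full effect of 0.5 SD from week 4 onward.* Power is 81% at rho 0.5 and 90% at rho 0.7.
- *Effect growing in proportion to time, reaching 0.5 SD at week 12.* The average effect is 0.5 × (4 + 8 + 10 + 12)/(4 × 12) = 0.354 SD. At rho 0.5 the standardised effect is 0.354/√0.375 = 0.578, against 0.5/√0.75 = 0.577 for week-12 ANCOVA, so both have about 52% power. At rho 0.7 it is 0.354/√0.285 = 0.663 against 0.5/√0.51 = 0.700, or about 62% against 67%.

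The large gain from averaging exists only if the effect is complete by week 4, halfway through the eight treatment weeks.

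**The case against.** The best defence is that nothing named is invalid. Under randomisation a t-test for a continuous index and a rank-sum test for an ordinal grade are fair comparisons, and chance baseline imbalance costs precision without adding bias. An article may also leave the covariates, the main visit and multiplicity for secondary outcomes to a fuller document. That is why the point rests on what the article does fix: which tests are the main ones, and where the mixed model is placed. A fuller plan that followed those choices would carry the same weakness.

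Some stronger readings are tempting but not supported:

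- *The plan ignores the baseline altogether.* The text is silent on raw or change scores, and change scores are not excluded. A t-test on each patient's mean over visits would even combine the visits. What holds is that neither test can adjust for the baseline as a covariate.
- *Power is lost and error is inflated at the same time.* These are alternatives. Power near 41% belongs to one visit tested once. The inflated error belongs to counting any of four visits, and that rule has higher power (about 72% at rho 0.5 on raw values).
- *The false-positive rate is 13-18%.* That needs rho of 0.7 or less when raw values are tested. Visits 2-4 weeks apart in patients at least three months from diagnosis, with missing values carried forward, could correlate more strongly.
- *Power would roughly double to 81%.* This requires the full effect from week 4. The Discussion itself says muscle improvement takes a long time.
- *The error rate applies to all three outcomes.* Only t-tests were simulated. The rank-sum test on H-B grade was not.

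**Conclusion.** The point holds as a matter of efficiency and of naming one answer per outcome, not as a claim that the tests are wrong.

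- At one visit, baseline adjustment moves power from about 41% (raw) or 31-61% (change) to 43-67%, for rho 0.3 to 0.7, 25 per arm and a 0.5 SD difference. The gain over raw values is small at rho 0.3 and large at 0.7. The gain over change scores runs the other way, from 12 points at rho 0.3 to 6 at 0.7.
- If every visit is tested at 0.05, the chance of at least one false positive is about 10-18% per continuous secondary outcome, for rho 0.9 to 0.3.

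Both sets of figures depend on assumed correlations. A reader might infer that the trial's overall error rate is compromised. It is not: this concerns secondary outcomes only and leaves the primary type I error untouched. The change is worth making because the data are already being collected and the plan already names a suitable class of model.

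**What to change.** In Data processing and statistical analysis, replace the sentence on the secondary tests with wording to this effect:

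- *LL-index and S-index:* main analysis on the FAS by a linear mixed model with group, visit, group-by-visit and baseline value. The between-group difference at one pre-named visit is the single main estimate, and the other visits are descriptive.
- *H-B grade:* ordinal model at the same visit, adjusted for baseline grade, combining sparse grades if needed.
- *t-test and Wilcoxon rank-sum test:* kept as unadjusted supporting analyses, stating whether raw or change scores are used.

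The sponsor should choose the visit before the planned interim analysis and before any other unblinded look. The four-visit average should not be the main estimate, because it dilutes an effect that builds over time.

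**Cost.** No new patients, visits or measurements. There is slightly more analysis work, reliance on the proportional-odds assumption for H-B grade with about 25 per arm, and the formal application that the article requires for protocol modifications. The sponsor should confirm that the named software version fits the ordinal model.
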